## Abstract

**Background:**

A protective or ultra-protective tidal volume strategy is widely applied to patients with acute respiratory distress syndrome (ARDS). The use of very low tidal volume has the potential to further redece ventilation-induced lung injury (VILI) comparde with a “normal” lung protective management. Plus, cardiogenic pulmonary edema (CPE) caused by hydrostatic mechanisms in patients with cardiogenic shock has similar respiratory mechanics to those found in patients with ARDS. And no consensus exists on mechanical ventilation parameter settings in patients with VA-ECMO. The study aimed to investigate the impact of an ultra-protective tidal volume strategy on the 28-day ventilator-free day (VFD) number in VA-ECMO–supported patients with refractory cardiogenic shock, including cardiac arrest.

**Methods:**

The Ultra-ECMO trial is a randomized controlled, open-label, single-center prospective superiority trial. At the onset of ECMO initiation, we will divide patients randomly into an intervention group and a control group in a 1:1 ratio. The control group will adopt protective ventilation settings [initial tidal volume: 6 ml/kg of predicted body weight (PBW)] for ventilation, and the intervention group will adopt ultra-protective ventilation settings (initial tidal volume: 4 ml/kg of PBW) for ventilation. The procedure is expected to last 72 h, after which the ventilator settings will be at the intensivists' discretion. The primary outcome is the VFD number at 28 days after inclusion. The secondary outcomes will include respiratory mechanics; analgesic/sedation dosage; lung ultrasound score; interleukin-6, interleukin-8, and monocyte chemotactic protein-1 levels in broncho-alveolar lavage fluid at the moment of enrollment (T0), 24, 48, and 72 h (T1, T2, and T3, respectively) after ECMO initiation; total time (in days) required for ECMO weaning; length of stay in the intensive care unit; total cost of hospitalization; amounts of resuscitative fluids; and in-hospital mortality.

**Discussion:**

VA-ECMO–treated patients without ARDS possess abnormal lung function. CPE, thoracic compliance reduction, and poor pulmonary blood perfusion are frequently present, and these patients can more easily progress to ARDS. It seems that targeting the protective tidal volume can lower adverse outcome incidence rates, even in patients without ARDS. This trial seeks to answer the question of whether adopting an ultra-protective tidal volume strategy can lead to superior primary and secondary outcomes compared to adopting a protective tidal volume strategy in patients treated by VA-ECMO. The Ultra-ECMO trial will provide an innovative mechanical ventilation strategy for VA-ECMO–supported patients for improving treatment outcomes at biological and potentially clinical levels.

**Clinical Trial Registration:**

ChiCTR2200067118.

## Introduction

1.

Refractory cardiogenic shock (RCS), including cardiac arrest (CA), is characterized by severe circulation failure accompanied by cardiogenic pulmonary edema (CPE) and often necessitates invasive mechanical ventilation (IMV) (1). In the most severe cases of RCS, veno-arterial extracorporeal membrane oxygenation (VA-ECMO) is a viable therapy used to maintain a certain amount of cardiac output (2). Although advances in VA-ECMO technology have significantly improved the clinical outcomes of patients suffering from RCS or CA in the past decades (3), there is a paucity of high-grade scientific evidence suggesting the optimal ventilator settings during VA-ECMO treatment. The Extracorporeal Life Support Organization has proposed a ventilation strategy with a positive end-expiratory pressure (PEEP) of ≥10 cmH_2_O and low minute ventilation without offering further specific details (4). In a recent observational study of 256 out-of-hospital CA (OHCA) patients, a decrease of 1 ml/kg PBW in the tidal volume (VT) during the first 48 h of intensive care unit (ICU) admission after OHCA was associated with a 61% increase in adjusted favorable neurocognitive outcomes, suggesting that a lower VT in the early phase of ICU admission may influence patient prognosis (5). However, a similar relationship has not been found among in-hospital CA patients (6).

To date, studies have advocated for the application of an ultra-protective VT strategy in patients with ARDS being treated by veno-veno ECMO (VV-ECMO) (7–9). Of note, CPE caused by hydrostatic mechanisms in patients with cardiogenic shock may have similar respiratory mechanics to those seen in patients with ARDS, although the pathophysiology is different. Similarly, IMV during VA-ECMO with ultra-protective VT may attenuate ventilator-induced lung injury due to the increased strain/stress and mechanical power transmitted by the ventilator. Thus, we hypothesized that adopting an ultra-protective VT strategy during the early phase of VA-ECMO may be a credible option to facilitate IMV weaning and even reduce in-hospital mortality. The results of this randomized controlled trial may subsequently add a novel and viable treatment solution to routine clinical practice involving VA-ECMO patients.

## Methods and analysis

2.

### Trial design

2.1.

Ultra-ECMO trial is a single-center, prospective clinical trial that will enroll 2 parallel groups of patients in a 1:1 ratio. It is designed to evaluate the 28-day number of ventilator-free days (VFDs) following an early, short-course application (72 h) of an ultra-protective VT vs. protective VT strategy in patients on VA-ECMO (Table 1) (1). Table 2 overviews the trial registration information. This trial protocol conforms to the Consolidated Standards of Reporting Trials (CONSORT) statements (10, 11) and has obtained the approval of the Research Ethics Committee at the First Affiliated Hospital of Nanjing Medical University. The legal guardians of eligible patients will sign the informed consent following the Declaration of Helsinki of 1964 (revised in 2013) (12).

**Table 1 T1:** Indications and contraindications for VA-ECMO.

Indications for VA-ECMO
1. Extracorporeal cardiopulmonary resuscitation (ECPR)
2. Acute myocardial infarction
3. Acute myocarditis
4. Progression of cardiomyopathy, ischemic or nonischemic
5. Acute RV failure due to pulmonary embolism
6. Progression of RV failure due to pulmonary disease
7. Progression of congenital heart disease
8. Primary graft failure and acute allograft rejection after heart transplantation
9. Overdose of cardiotoxic drugs
10. Septic cardiomyopathy
11. Trauma
12. Refractory ventricular tachycardia
13. RV failure during LVAD support
14. Failure to wean off cardiopulmonary bypass
Contraindications for VA-ECMO
1. Severe irreversible noncardiac organ failure limiting survival (e.g., severe anoxic brain injury or metastatic cancer)
2. Irreversible cardiac failure if transplantation or long term LVAD are not considered
3. Aortic dissection
4. Severe coagulopathy or contraindication to anticoagulation, including advanced liver disease
5. Limited vascular access (severe peripheral arterial disease, extreme obesity, amputated limbs, among others)

LVAD, left ventricular assist device; VA-ECMO, veno-arterial extracorporeal membrane oxygenation; RV, right ventricular.

**Table 2 T2:** The trial registration for the ultra-ECMO trial.

Data category	Information
Primary registry and trial identifying number	ChiCTR2200067118
Trial protocol version	Version 1
Source of monetary or material support	The National Natural Science Foundation of China
Primary sponsor	The National Natural Science Foundation of China
Secondary sponsor	N/A
Contact for public queries	[name], [contact] YM, [contact] [name], [contact]
Public title	Randomized Controlled Trial of Ultra-Protective vs. Protective mechanical ventilation strategy in veno-arterial Extracorporeal membrane oxygenation patients with Refractory cardiogenic shock: study protocol for the Ultra-ECMO trial
Country	China
Study type	Type: Randomized controlled, parallel group, clinical trial Group allocation: Simple randomization Masking: data analyst, statistician blinded
Date of first enrollment	Not yet started
Target sample size	614 in total
Primary outcome(s)	The 28-day ventilator-free day
Key secondary outcome(s)	All-cause in-hospital mortality, level of nflammatory factors in BAL, time to VA-ECMO weaning, length of ICU stay,respiratory mechanics parameters, lung ultrasound score, total analgesic/sedation dosage, total cost for hospitalization, amounts of fluid resuscitation

### Trial objectives

2.2.

This trial has the main objective of assessing the potential benefit of an ultra-protective VT strategy relative to a protective VT strategy on the 28-day VFD number (13) (Table 3).

**Table 3 T3:** Ready for invasive mechanical ventialtion weaning checklist.

Step 1: Patient's clinical condition is appropriate for attempting to decrease the level of respiratory support, e.g.: without severe shock or multi-organ failure
Step 2: Patient is awake enough to at least protect his or her airway, cooperative enough not to be at significant risk for dislodgement of cannulas or other important catheters or devices, and not requiring heavy or frequent sedation
Step 3: Secretions are manageable without an artificial airway
Step 4: The patient should have an acceptable arterial blood gas on minimal ventilator settings (e.g.: FiO2 0.4, PEEP 5):Goal PaO2 > 80 mmHg, pH > 7.35 with minute ventilation < 10 L/min
Step 5: Weaning of mechanical ventilation

FiO2, fraction of inspired oxygen; PEEP, positive end-expiratory pressure; PaO2, partial pressure of arterial oxygen.

Meanwhile, the secondary objectives of this study include the following:
1.To examine whether ultra-protective VT can decrease the all-cause in-hospital mortality rate2.To examine whether ultra-protective VT can reduce the time for successful VA-ECMO weaning (Table 4)3.To examine whether ultra-protective VT is associated with a shorter ICU length of stay4.To examine whether ultra-protective VT is associated with a reduction in interleukin-6 (IL-6), interleukin-8 (IL-8), and monocyte chemotactic protein-1 (MCP-1) levels in broncho-alveolar lavage fluid (BALF)5.To examine whether ultra-protective VT affects respiratory parameters (e.g., total PEEP, plateau pressure [P_plat_], driving pressure [DP], airway resistance [R], static compliance [C_stat_], mean airway pressure [P_mean_], esophageal pressure [P_es_], transpulmonary pressure [P_tp_], and mechanical power [MP]), based on a daily assessment from inclusion to closeout (14)6.To examine whether the ultra-protective VT strategy decreases the lung ultrasound score (LUS) (Figure 1 and Table 5) when assessed daily from inclusion to closeout (15, 16)7.To examine whether ultra-protective VT can lead to an increased analgesic/sedation dosage during the intervention period after inclusion8.To examine whether ultra-protective VT predicts a decrease in the total hospitalization cost9.To examine whether ultra-protective VT is associated with a reduced demand for fluid resuscitation

**Figure 1 F1:**
[figure not shown]
Lung ultrasound regions. PSL, parsternal line; AAL, anterior axillary line; PAL, posterior axillary line; PVL, paravertebral line.

**Table 4 T4:** Ready for VA-ECMO weaning checklist.

VA ECMO weaning should be considered when patients exhibit stable hemodynamics with reduced ECMO flow, even if n low doses vasoactive or inotropic Support is mandatory
1. MAP > 60 mmHg
2. LVOT VTI > 0.12 m/s
3. Tissue Doppler lateral mitral annulus peak systolic velocity ≥6 cm/sec
4. CVP ≤ 10 mmHg, and LV ejection fraction ≥25%–30% on low doses vasoactive, inotropic support.
5. All the above mentioned conditions are fulfilled indicating the patient is readey for VA-ECMO weaning

VTI, velocity time integral; CVP, central venous pressure; LVOT, left ventricular outflow tract; MAP, mean arterial pressure.

**Table 5 T5:** Calculaiton of lung ultrasound score (LUS).

	Aeration	Lung ultrasound appearance
Score 0	normal	A lines-max 2 B lines
Score 1	moderate loss	B1 lines (≥3 well-spaced B lines with horizontal spacing between adjacent B lines ≤7 mm)
Score 2	severe loss	B2 lines (multiple B lines fused with horizontal spacing between adjacent B lines ≤3 mm)
Score 3	complete loss	echoic lung tissue, accompanied by dynamic air bronchogram
Total score		Global LUS was calculated by summing the highest score of each region (0–36)

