### Data collection and management

2.7.

The total duration of ECMO treatment, total time (in days) on IMV, ICU length of stay, analgesic/sedation dosage, all-cause hospital mortality, levels of inflammatory factors in BALF, LUS, amounts of fluid infusion, and total hospitalization cost will be calculated using patient medical records (Table 6).

**Table 6 T6:** Scheduled events and timeline for the ultra-ECMO trial.

		Study period					
Timepoint		Eligibility/Allocation	Post-Allocation			Close-out	
		T0 ECMO initiation	T1 24 h after ECMO	T2 48 h after ECMO	T3 72 h after ECMO	T4 28 days after ECMO	Tx ICU discharge day
Enrollment	Eligibility check	×					
	Informal consent	×					
	Allocation	×					
Intervention	Ultra-protective or protective VT group	×					
Assessments	Demorgraphic data	×					
	Comorbidity	×					
	Clinical characteristics	×					
	Respiratory mechanics parameters	×	×	×	×		
	LUS	×	×	×	×		
	Levels of inflammatory factors in BALF	×	×	×	×		
	In-hospital mortality		×	×	×	×	×
	RASS score	↔					
	VIS	↔					
	Amounts of resuscitative fluids		×	×	×	×	×
	Sedation and NMBA dose	↔					
	ICU LOS	↔					
	Total length of ECMO weaning	↔					
	Total lenght of IMV weaning	↔					
	Total cost for hospitalization						×
	Total hospital LOS	↔					
	28-day VFD	↔					

VT, tidal volume; VFD, ventilator-free day; ICU, intensive care unit; LOS, length of stay, VIS, vasoactive inotrope score; RASS, richmond agitation sedation scal; LUS, lung ultrasound score; BALF, broncho-alveolar lavage fluid.

We will not consider missing values for primary and secondary outcomes during hospitalization. However, missing values could appear specific to patients who survive to hospital discharge. If so, we will contact patients or their next of kin at day 28 to assess the pre-defined outcomes.

Clinical data will include but are not limited to general characteristics (age, sex, weight, height), comorbidities, original disease, the Acute Physiology and Chronic Health Evaluation II score, partial pressure of arterial oxygen/inspired oxygen fraction, PEEP, VT (in ml/kg of PBW), respiratory rate (in breaths/min), DP, P_plat_, P_es_, P_tp_, P_mean_ (in cm of water), C_stat_ (in ml/cmH_2_O), R (in cmH_2_O/L/s), arterial blood PaO_2_ and PaCO_2_ values (in mmHg), and mechanical power (in J/min).

We will also monitor the clinical conditions as well as the ECMO running status and collect any records.

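### Table 4 gives the LVOT velocity time integral threshold for VA-ECMO weaning in m/s, a velocity unit, although the quantity is a length

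*Protocol article*

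**What the plan says.** Table 4 in section 2.2 of the protocol article is a checklist for readiness to wean from VA-ECMO. Item 2 reads "LVOT VTI > 0.12 m/s", and the footnote under the table spells out "VTI, velocity time integral". Item 3, the next line, is "Tissue Doppler lateral mitral annulus peak systolic velocity ≥6 cm/sec".

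The table opens as guidance: "VA ECMO weaning should be considered when patients exhibit stable hemodynamics with reduced ECMO flow". Its item 5 then treats a patient as ready when every condition above it is met, so item 2 is one part of an all-must-hold rule.

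The table is tied to an objective. Secondary objective 2 asks whether the ultra-protective strategy can "reduce the time for successful VA-ECMO weaning (Table 4"). The corresponding outcome appears in the Abstract (Methods) as "total time (in days) required for ECMO weaning" and among the key secondary outcomes in Table 2 as "time to VA-ECMO weaning". Section 2.7 says that ECMO duration, with the other listed outcomes, "will be calculated using patient medical records".

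**The concern.** The quantity named in item 2 and the unit attached to it do not agree. By the footnote's own expansion the quantity is a velocity accumulated over time, which is a distance. The printed unit, m/s, is that of a velocity.

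The number is a stated decision threshold in the Methods, in a checklist that a secondary objective cites, and not an incidental figure in background text. Anyone applying the checklist literally has a reading in cm and a cut-off in m/s, and must guess what was meant before deciding whether the item is satisfied. What is at stake is whether one readiness criterion is applied clearly and consistently at the bedside. The comparison of the arms on the primary outcome is not at stake.

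**Working it through.** **Inputs**, all from Table 4 and its footnote:
- threshold as printed: more than 0.12 m/s (item 2)
- meaning of VTI: velocity time integral (footnote)
- neighbouring velocity criterion: at least 6 cm/sec (item 3)

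**Step 1. Dimension of the quantity.** VTI = ∫ v dt, so its unit is (m/s) × s = m. The printed unit is m/s. The two differ by a factor of time, so no change of scale (m to cm, for example) can reconcile them.

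**Step 2. The two readings of the printed number.**
- As printed: 0.12 m/s × 100 = 12 cm/s, a velocity, which is not a possible unit for a VTI.
- With the "/s" removed: 0.12 m × 100 = 12 cm, a length, which is a possible unit for a VTI.

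Dropping two characters makes the entry dimensionally correct, so a slip in the unit is the evident explanation.

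**Step 3. Could it be an artefact of text extraction?** The line is intact, with a clean number and a clean unit. Item 3 names a true velocity and gives it correctly in cm/sec. The table therefore assigns a velocity unit to two different kinds of quantity, and is right only for item 3.

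**Step 4. Is the threshold given elsewhere?** No other part of the article states a VTI cut-off, in length units or otherwise, so nothing in the text settles the intended value.

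**Step 5. What a literal reading would imply (illustration only).** Suppose a reader took 0.12 m/s as a mean velocity over ejection. The article gives no ejection time. Assuming 0.2 to 0.4 s, the implied VTI is 12 cm/s × 0.2 s = 2.4 cm up to 12 cm/s × 0.4 s = 4.8 cm, against 12 cm under the evident reading. This shows that the two readings are far apart. It does not show that anyone would adopt the literal one, and the finding does not depend on it.

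**Step 6. Reach of the error.** The sample size in section 2.8 uses only the assumed means (7.1 and 9.2), standard deviations (8.8 and 9.3), α and power for ventilator-free days. Those inputs do reproduce the stated 292 per group at 80% power. The threshold does not enter that calculation or the analyses in section 2.9.

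**The case against.** The best case on the other side is that this is a copy-edit slip with almost no consequence. An experienced echocardiographer would read the entry as 12 cm, the checklist applies equally to both arms, and no outcome or analysis uses the number. That stands, and it is why the point is rated minor. It does not make the entry correct: that an error is easy to spot lowers its weight but does not remove it.

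A second objection is that the article shows only a mismatch between quantity and unit. It does not show which of the two is wrong, or that 12 cm was intended. This also stands. Confidence is high for the mismatch; the replacement value is an inference that the sponsor has to confirm.

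A third is that calling the checklist advisory and separate from the outcome goes a little further than the text. Item 5 is worded as a firm rule, and section 2.7 says where ECMO duration comes from without saying what makes weaning successful, a phrase to which objective 2 attaches Table 4. That is a fair caution. Even if the checklist did shape when patients are weaned, it would do so by the same rule in each arm, and the article gives no basis for claiming a difference between them.

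**Conclusion.** The point holds. Item 2 of Table 4 is dimensionally wrong as written, on the table's own definition of VTI, and nothing in the article corrects it. The conclusion needs no outside source and no assumption beyond the meaning of an integral over time.

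Its size is one wrong unit in one table entry. The practical risk is small because the number fits the evident reading of 0.12 m (12 cm). That reading is the only inferred element. No bias, and no effect on any primary or secondary outcome, is shown or claimed. Severity: minor.

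**What to change.** In Table 4, item 2, state the threshold as a length: apparently an LVOT VTI above 12 cm (0.12 m). The sponsor should confirm the value against the source of the checklist before it is changed, and should confirm at the same time that VTI is the parameter intended.

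The cost is one unit in one table, with no effect on the sample size, error rate or analyses. Table 2 records that enrolment had not begun at the time of writing; if that is still so, the change can be made before the first patient. If recruitment is under way, a short clarification to the clinical team would do.

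As an optional and separate clarification, the ejection-fraction entry in item 4 gives a range (25% to 30%) as its lower limit. The investigators could name a single cut-off or say that the range is left to clinical judgement.

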### Interventions

2.6.

At the onset of ECMO initiation, all participants will be screened by therapists. Once the patient meets the inclusion criteria and is finally enrolled, the therapists will provide the selected intervention. We will assign patients in the intervention group to receive ultra-protective VT after randomization (initial settings: VT, 4 ml/kg of PBW; PEEP, 10 cmH_2_O; respiratory rate, 10 min^−1^; Vt may be decreased stepwise by 0.5 ml/kg PBW if the plateau pressure is >30 cmH_2_O) (17).

Patients in the control group will be managed using a protective VT strategy after randomization (initial settings: VT, 6 ml/kg of PBW; PEEP, 10 cmH_2_O; respiratory rate, 10 min^−1^; Vt may be decreased stepwise by 0.5 ml/kg of PBW if the plateau pressure is >30 cmH_2_O).

We will set the sweeping gas flow of ECMO, targeting a PaCO_2_ range of 35–45 mmHg, and the FiO_2_ value of the ventilator may be increased if PaO_2_ in the right upper limb decreases to <60 mmHg during the course of Vt and PEEP adjustments.

Furthermore, a hybrid veno-arterio-venous ECMO mode will be considered if differential oxygenation happens (18). Differential oxygenation refers to the lower body being perfused by ECMO-oxygenated blood while the upper body (coronaries, right arm, brain) receives hypoxemic blood pumped by the native heart. This pathophysiological phenomenon often results from the recovery of native left ventricular function and simultaneous severe lung failure. If optimized ventilation fails to solve this issue, it will be necessary to employ veno-arterio-venous ECMO in consideration of the potential for hypoxic damage to the brain and heart (19, 20).

At the moment of enrollment (T0), investigators will take charge of assessing and collecting pre-defined respiratory mechanics parameters; IL-6, IL-8, and MCP-1 levels; LUS; and other trial data as baseline information. The same procedure will be performed repeatedly at 24, 48, and 72 h (T1, T2, and T3, respectively) after ECMO initiation (Figure 2). After 72 h, the mechanical ventilation strategy in both groups will be changed at the intensivists' discretion.

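### Table 5 leaves two lung ultrasound patterns without a score and ties score 3 to a breath-dependent sign, while the arms are ventilated at different tidal volumes

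*Protocol article*

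**What the plan says.** Secondary objective 6 (section 2.2) reads "To examine whether the ultra-protective VT strategy decreases the lung ultrasound score (LUS"), so a lower score in the intervention arm counts as benefit. Table 5 sets four classes per region:

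- The top class, score 3, stands for lung that has lost all its air and is worded as "echoic lung tissue, accompanied by dynamic air bronchogram".
- The bottom class, score 0, allows A lines and no more than two B lines.
- Between them, score 1 asks for "B1 lines (≥3 well-spaced B lines with horizontal spacing between adjacent B lines ≤7 mm").
- The other middle class, score 2, asks for fused lines no more than 3 mm apart.

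The regions are then added up, and the table gives the rule as "Global LUS was calculated by summing the highest score of each region (0–36").

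Section 2.6 and Table 6 place LUS at T0 and at 24, 48 and 72 h. Over that period the intervention arm starts from "initial settings: VT, 4 ml/kg of PBW; PEEP, 10 cmH_2_O" and the control arm from "initial settings: VT, 6 ml/kg of PBW; PEEP, 10 cmH_2_O", with the same initial respiratory rate. Section 2.5 says that outcome assessors will not know the allocation. Section 2.9.3 compares LUS between arms by t test or Mann–Whitney test.

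**The concern.** A score summed over regions needs every region to fall into a class. Table 5 leaves two patterns without one, so readers must improvise, and the total then depends partly on individual habit.

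The gap at score 3 raises a further question. In its ordinary meaning, which the document does not spell out, a dynamic air bronchogram is air seen moving in the airways with the breath. Breath size is what the trial randomises. If the sign appears more or less often at one tidal volume than at the other, the same airless region could be scored differently in the two arms although aeration is equal. That would put a measurement artefact into the comparison that objective 6 sets out to make.

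**Working it through.** **The plan's own figure.** The only LUS figure stated is the range 0–36. At 0–3 per region this implies 36 / 3 = 12 regions. Figure 1, which shows the regions, is not reproduced in the text at hand, so 12 is an inference.

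**Patterns set against the rows of Table 5, read literally.**

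| Pattern | Rows met |
|---|---|
| 2 B lines, 10 mm apart | 0 |
| 3 B lines, 10 mm apart | none: too many lines for 0, too far apart for 1 |
| 4 B lines, 8 mm apart | none, for the same reason |
| 3 B lines, 5 or 7 mm apart | 1 |
| 4 B lines, 2 or 3 mm apart | spacing limits of both 1 and 2 |
| Consolidation with dynamic bronchogram | 3 |
| Consolidation with static or no bronchogram | none |

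The overlap at 3 mm or less is largely settled by the table itself: score 1 describes separate lines, score 2 describes fused ones, and the highest score in a region counts. The two empty entries are not settled. The exclusions in section 2.4 cover blurry images, pneumothorax and massive pleural effusion, but neither of these patterns.

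**Is the score 3 gap relevant here?** Section 3 describes dense dependent regions in ARDS and reports that some patients with cardiogenic pulmonary edema show a similar gravity-dependent picture. Consolidated regions are therefore plausible in this population. The document does not say how common they are.

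**What an artefact would look like (illustration only).** Let

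- k = consolidated regions per patient,
- g = probability of seeing the dynamic sign in such a region in the control arm minus that in the intervention arm,
- s = score given when the sign is absent.

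With equal lungs, the artefactual mean difference (control minus intervention) is D = k × g × (3 − s). None of k, g, s or the LUS standard deviation is in the document; all are assumed.

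- k = 2, g = 0.2, s = 2: D = 2 × 0.2 × 1 = 0.4 points
- k = 2, g = 0.2, s = 0: D = 2 × 0.2 × 3 = 1.2 points
- k = 4, g = 0.3, s = 2: D = 4 × 0.3 × 1 = 1.2 points
- k = 4, g = 0.3, s = 0: D = 4 × 0.3 × 3 = 3.6 points

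Take 292 per arm and two-sided α = 0.05 (both from section 2.8) and an assumed SD of 6. The standard error is 6 × √(2/292) = 0.497. The chance of a significant result favouring the intervention arm is Φ(D/0.497 − 1.96): about 12% for 0.4 points, 68% for 1.2 points, and above 99% for 3.6 points. Over assumed SDs of 4 to 8, the 0.4-point case ranges from 23% to 9% and the 1.2-point case from 95% to 44%.

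**Where it vanishes or turns.** If g = 0, D = 0. If g is negative, D changes sign. If s = 3, because readers score consolidation as 3 regardless, D = 0 for any k and g. If such regions are set to missing, the direction is open.

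**The case against.** The strongest reply is that the aeration column labels score 3 as complete loss, so a reader facing airless, tissue-like lung has an obvious row whatever the bronchogram does. Scoring it 0 would call airless lung normal, which is the less natural error. The wording about the bronchogram may also be meant as description rather than as a requirement. This stands as a reason why the artefact may never occur. It does not make the rule sound, because the literal text adds a condition that some readers will apply.

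A reader might infer that the LUS comparison is biased toward the 4 ml/kg arm by 1 to 3 points, or that up to 12 points are at the reader's discretion through the spacing gap. The document does not support either. It nowhere says that the sign differs between 4 and 6 ml/kg, or how an unclassified region is scored. The 1 to 3 points simply restate an assumed difference of one region between arms. The 12 points need all 12 regions to show one pattern. For the spacing gap there is also no mechanism that would work differently by arm; with blinded assessors it adds noise.

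Blinding does not answer the score 3 point, because the sign is in the image itself and the definition refers to it.

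Finally, this is a condensed article. Figure 1 and the cited LUS references are not at hand, and reader instructions may sit in the full protocol, so their absence here is no fault. The criticism concerns only what Table 5 states.

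**Conclusion.** The point holds as a defect in a stated scoring rule. Table 5 gives no class to three or more B lines more than 7 mm apart, nor, on its literal wording, to consolidation without a dynamic air bronchogram. Because the second gap turns on a sign seen with the breath, a between-arm artefact is possible at 24, 48 and 72 h. It requires two things that the document does not establish: that the sign's frequency differs between the tidal volumes in use, and that readers score such regions below 3 or leave them out. Its size and direction are therefore unknown, and the 0.4 to 3.6 points above are illustrations, not estimates.

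The reach is limited. LUS is one of nine secondary objectives; the primary outcome, its analysis and the sample size do not depend on it. The rewording is still worth making, since it is cheap and removes the problem whichever assumptions are true.

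**What to change.** Reword Table 5 before the first patient is enrolled (Table 2 gives enrollment as not yet started):

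- Score 0: unchanged.
- Score 1: three or more distinct, non-fused B lines spaced more than 3 mm, with no upper spacing limit.
- Score 2: fused B lines, or spacing of 3 mm or less.
- Score 3: tissue-like consolidation, with or without an air bronchogram of any kind.
- Total: keep the sum of the highest score per region, 0–36.

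If the dynamic or static character of the bronchogram is of interest, record it as a separate descriptive item outside the score.

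With score 3 defined this way, s = 3 for every consolidated region, so D = 0 for any k and g. The score 1 wording is needed separately, because it is what closes the spacing gap.

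The cost is the text of one table and reader training, with no extra scans. The downside is slightly less comparability with series scored under the current wording.
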